### Participants

2.3

#### Source of population

2.3.1

Active duty U.S. Army soldiers assigned to Fort Cavazos (formerly Fort Hood), Texas, will be eligible to participate in the R2OE study. One unit that has already agreed to participate representing a military unit regularly scheduled to deploy to high-risk/high-threat environments is the 3rd Security Force Assistance Brigade (SFAB). SFABs are specialized Army units formed to train, advise, assist, enable, and accompany operations with allied and partner nations. They were created with the intent to reduce the burden of such operations on conventionally organized Brigade Combat Teams (BCTs), allowing BCTs to focus on fighting near-peer threats. Designed on the model of a standard infantry BCT, SFABs are composed of approximately 800 experienced senior personnel, primarily commissioned, warrant, and non-commissioned officers. They are selected from regular Army units and given additional training at the Military Advisor Training Academy at Fort Moore, Georgia. We will begin recruitment efforts with the 3rd SFAB. Should recruitment from SFABs prove insufficient, we will recruit from additional units stationed at Fort Cavazos, such as Brigade Combat Teams and other units that most closely resemble the SFABs in terms of military service characteristics.

### Recruitment & randomization

2.4

Soldiers are recruited through briefings at various unit meetings as well as at the unit’s Newcomers’ Briefing held monthly. Any soldier, 18 years or older, is eligible for inclusion. There are no exclusion criteria. Participants are equally randomized between the two groups stratifying for rank to ensure equal numbers of junior non-commissioned officers (NCOs; grades E-4 to E-6), senior NCOs (grades E-7 to E-9), and officers (warrant and commissioned) are in each group. In accordance with Department of Defense (DoD) Instruction 3216.02, participants can be compensated if study participation does not adversely impact their ability to perform their assigned duties. Five assessments are scheduled. Each time an assessment is completed, $25 can be compensated, for a total of $125.

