#### Randomization

2.2.1

Recruited personnel will be randomized as a group to Resilience Enhancement through Acceptance and Commitment Training (REACT) or regular programming. Group randomization will be completed prior to recruitment or consent. Groups will be randomized by a randomization list generated by the research team’s Biostatistics Core. The randomization list will use random blocks of 4, 6, and 8 to ensure roughly equal numbers of groups in each condition as the study progresses and to reduce the anticipation of group assignment and thereby the potential for bias.

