#### Power analysis

2.7.1

Statistical power estimates were obtained from the PASS15 software (NCSS, 2017) modules for comparison of two means or two proportions in a cluster randomized design. Estimates were obtained for a range of standardized mean differences (Cohen’s *d*) from 0.35 to 0.50, which range from modest (*d* = 0.35) to medium in size (*d* = 0.50). Effect sizes below 0.35 are unlikely to be clinically significant and *d* = 0.50 is often considered to be a threshold for a meaningful difference. We also estimated the reduction in Failure % that was detectable at 0.80 assuming a base rate of 80%. We specified a total of 12 clusters of 50 participants for a total *N* = 600. The proposed sample size (*N* = 600) provides statistical power of at least 80% to detect a standardized mean difference (or change over time) in the “small to moderate” range (Cohen’s *d* of 0.30). This applies not only to analyses involving the entire randomized sample but also for analyses based on subsamples based on factors such as deployment, demographics, or other military service characteristics.

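### The article gives two incompatible units of randomization: whole groups allocated before recruitment (2.2.1, 2.7.1) and individual participants stratified by rank (2.4)

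*Protocol article*

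**What the plan says.** Section 2.2.1 (Randomization) makes the group the unit: "Recruited personnel will be randomized as a group to Resilience Enhancement through Acceptance and Commitment Training (REACT) or regular programming". It fixes the timing: "Group randomization will be completed prior to recruitment or consent". The list uses "random blocks of 4, 6, and 8 to ensure roughly equal numbers of groups in each condition", and no stratification factor is named.

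Section 2.7.1 (Power analysis) agrees with this. It uses software "modules for comparison of two means or two proportions in a cluster randomized design" and adds: "We specified a total of 12 clusters of 50 participants". It concludes that N = 600 gives at least 80% power at d = 0.30. No ICC is stated.

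Section 2.4 (Recruitment & randomization) describes something else: "Participants are equally randomized between the two groups stratifying for rank to ensure equal numbers of junior non-commissioned officers". The ranks listed are E-4 to E-6, E-7 to E-9, and warrant and commissioned officers. The same paragraph admits any soldier aged 18 or over, with no exclusions.

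Section 2.7 defines the intent-to-treat set as all randomized participants. It names fixed effects of arm, time and their interaction, with deployment history as a covariate. Random intercepts and slopes are to be tested, but their level is not given. Section 2.8 also speaks of participants being randomized to the intervention arm.

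**The concern.** Rank belongs to the individual. If whole groups are allocated before anyone is approached, enrolment decides afterwards how many of each rank end up in each arm. The allocation list cannot then deliver the balance that section 2.4 promises. If individuals are allocated within rank strata, section 2.2.1 and the cluster power calculation do not describe the trial.

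This is more than wording, because several things depend on the unit:

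- **Primary test.** Under group allocation its standard error must reflect variation between groups.
- **Power statement.** The same N = 600 means something different under each unit.
- **Intent-to-treat set.** If groups are allocated before consent, no individual is randomized, so the set needs a definition.
- **Main threat to validity.** It is selective enrolment after a known group allocation in one case, and contamination between arms within a unit in the other.

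A smaller gap is that the rank strata start at E-4, so an eligible soldier at E-1 to E-3 belongs to no stratum.

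**Working it through.** **Can the sections describe one procedure?** One could read 2.4 as allocation of groups with rank balanced at group level. Two things prevent this. The list in 2.2.1 balances only the count of groups and names no rank factor. And a list applied before consent cannot ensure equal numbers by rank among those who later enrol. The two descriptions remain incompatible.

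**What depends on the unit.** Inputs from the article: N = 600, 300 per arm, 12 clusters of 50, d = 0.30 (SD = 1), two-sided alpha 0.05. The ICC is not given; 0.01, 0.02 and 0.05 are assumptions.

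Formulas:
- Individual: SE = √(2/300) = 0.0816; 0.30/SE = 3.674; power = Φ(3.674 − 1.960) = Φ(1.714) = 0.957.
- Cluster: DEFF = 1 + (50 − 1) × ICC; effective N = 600/DEFF; noncentrality = 3.674/√DEFF. Power is taken from the normal distribution and from a noncentral t with 12 − 2 = 10 df.
- Type I error if groups are randomized but clustering is ignored: 2 × [1 − Φ(1.960/√DEFF)].

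| Unit | ICC (assumed) | DEFF | Effective N | Noncentrality | Power, normal | Power, t 10 df | Type I error, clustering ignored |
|---|---|---|---|---|---|---|---|
| Individual | none | 1.00 | 600 | 3.674 | 0.957 | n/a | 0.05 |
| Group | 0.01 | 1.49 | 402.7 | 3.010 | 0.853 | 0.774 | 0.108 |
| Group | 0.02 | 1.98 | 303.0 | 2.611 | 0.743 | 0.654 | 0.164 |
| Group | 0.05 | 3.45 | 173.9 | 1.978 | 0.507 | 0.432 | 0.291 |

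**The plan's own figure.** The 80% at d = 0.30 cannot be reproduced uniquely without an ICC. With individuals it is met with room to spare: 175 per arm, 350 in all, would be enough. With 12 × 50 and the normal approximation, exactly 80% requires DEFF = (3.674/2.802)² = 1.72, so ICC = 0.72/49 = 0.0147. A root search with the t distribution on 10 df gives 0.0081.

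**The case against.** The strongest reply is that this is a condensed article. The ICC and the level of the random effects are details usually left to a fuller document, so their absence is no error. That is right, and neither omission is charged here. It does not remove the contradiction, because the article states two different units outright.

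The reply also limits what a reader might infer:

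- **That the power statement is false.** This is not shown. It holds for individual randomization, and for 12 clusters if the ICC is small enough. The cluster figures rest on assumed ICCs and on a single mean comparison, and take no account of any precision gained from repeated measures.
- **That the analysis model is wrong.** Section 2.7 names no cluster term but does not exclude one. The type I error figures apply only if groups are randomized and clustering is in fact ignored.
- **That the blocks fail because they do not guarantee a 6:6 split.** Section 2.2.1 promises only roughly equal numbers of groups. The 12 clusters are a planning figure, not a stated list length.
- **That the plan wrongly believes allocation has balanced deployment.** No section claims this, and deployment history enters the model as a covariate.
- **That the groups should be re-allocated in matched or fixed blocks.** The article varies block sizes so that assignments are harder to anticipate, and such a scheme would give that up.

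The E-1 to E-3 gap is also minor while recruitment stays in the SFAB, which section 2.3.1 describes as mainly officers and NCOs. It becomes practical if the fallback units, such as Brigade Combat Teams, are used.

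**Conclusion.** The contradiction stands and must be resolved, because the primary comparison cannot be analysed or its power judged until the unit is known. The rank balance promised in 2.4 cannot follow from the procedure in 2.2.1.

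At d = 0.30 the choice of unit separates power of about 0.96 from a range of 0.85 down to 0.43, for assumed ICCs of 0.01 to 0.05 and depending on the reference distribution. The stated 80% survives under group allocation only if the ICC is at most about 0.015 (normal) or 0.008 (10 df). If clustering were ignored under group allocation, the nominal 5% test would run at about 11% to 29% over the same ICCs. All cluster figures assume 12 equal groups of 50, six per arm. The article does not show which unit is in use, so this review does not choose one.

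**What to change.** State the unit of randomization actually used, and make 2.2.1, 2.4, 2.7 and 2.7.1 agree with it.

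- **If it is the group:** remove the rank sentence in 2.4, or restate it as balance at group level or as covariate adjustment for individual rank. Specify a random effect for the randomized group with small-sample degrees of freedom. Define the intent-to-treat set for people enrolled after their group was allocated. Restate the power with its ICC.
- **If it is the individual:** remove the group-randomization text. Stratify by rank with a stratum that covers E-1 to E-3, include rank in the model, and restate the power for individual randomization.

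The cost is mainly wording, plus one extra model term and a rerun of the power calculation. Under group allocation the restated power may fall below 80% at d = 0.30. The detectable d at 80% power (normal) is 2.802 × √(DEFF × 2/300), which gives 0.28, 0.32 or 0.42 at ICC 0.01, 0.02 or 0.05. The sponsor would then have to accept a larger detectable effect or enlarge the design.

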### Data analytic plan

2.7

The primary outcome to address study aims is the change score difference between group (psychological flexibility vs. treatment as usual) on the Connor-Davidson Resilience Scale (CD-RISC) over time. Analyses will be intent-to-treat using data from all randomized participants regardless of the extent of participation. The statistical analysis model is a mixed-effects regression with repeated measures using all assessment time points. Advantages of likelihood-based regression models over conventional ANOVA include the ability to use data from all participants even if they only have baseline data, relaxation of the assumption of equal variances, specification of data distributions other than normal, and the ability to analyze longitudinal data in the presence of missing data. Models will include the fixed effects of group, time, and the respective two-way interaction. Deployment history will also be entered into models as a covariate. Random intercepts and slopes will be tested, and covariance structure selection will be based on likelihood criteria model comparisons (e.g., Akaike’s Information Criteria). Little’s (1988) missing completely at random test and regression-based sensitivity analyses will be used to investigate the nature of missingness and the appropriateness of likelihood-based modeling (54). We will also derive and report on minimally important difference metrics on the CD-RISC (55, 56). Supplementary analyses of the other measures will use the same statistical analysis design. We will report on minimally important change and reliable change indices for the Posttraumatic Stress Disorder Checklist-5 (PCL-5), for which these metrics have been established (55, 57). We will assess deployment history at all time-points and will use this as a covariate in all pre-post analyses. All tests will be two-tailed with unadjusted *p* = 0.05. Analyses will be done using the LME4 package using R statistical software.

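### Rank is a stratification factor but not a term in the stated model, and its three bands have no place for eligible soldiers below E-4: minor, and cheap to put right

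*Protocol article*

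**What the plan says.** Section 2.4 (Recruitment & randomization) states: "Participants are equally randomized between the two groups stratifying for rank". The aim is equal numbers of junior NCOs (E-4 to E-6), "senior NCOs (grades E-7 to E-9), and officers (warrant and commissioned) are in each group". The same paragraph sets eligibility: "Any soldier, 18 years or older, is eligible for inclusion", followed by "There are no exclusion criteria".

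Section 2.7 (Data analytic plan) specifies the model: "Models will include the fixed effects of group, time, and the respective two-way interaction". Deployment history is added as a covariate, and random intercepts and slopes are to be tested. Rank is not mentioned. The other outcome measures are to be analysed in the same way. The primary outcome is the between-group difference in change on the CD-RISC.

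Three other places bear on the point:

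- Section 2.2.1 (Randomization) describes a different scheme. Groups are randomised before recruitment or consent, in blocks of 4, 6 and 8 that balance the number of groups. Rank does not appear there.
- Section 2.3.1 (Source of population) describes the first brigade: "SFABs are composed of approximately 800 experienced senior personnel, primarily commissioned, warrant, and non-commissioned officers". If recruitment there falls short, "we will recruit from additional units stationed at Fort Cavazos, such as Brigade Combat Teams", along with other units chosen for their likeness to the first.
- Section 2.7.2 (Addressing hypotheses) restricts the second research question to deployed participants.

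**The concern.** A factor used to constrain the randomisation normally belongs in the analysis. Stratifying removes chance differences in rank between the arms. A model that ignores rank still counts the rank-related spread as noise, so its standard error is too large for the design. Here the article names one covariate and leaves out the one that the allocation rule uses.

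The allocation rule is also incomplete as written. An adult soldier at E-1 to E-3 meets the eligibility rule and falls in no band.

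What is at stake is a little precision, a test that may run slightly below its nominal level, chance rank imbalance where the design does not control it, and an allocation rule that does not say what to do with some eligible soldiers.

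**Working it through.** **The plan's own figure.** The article gives no figure that involves rank. Its power statement (section 2.7.1) is at least 80% for d = 0.30 with N = 600, as 12 clusters of 50. Ignoring clustering, 300 per arm gives 95.7%, and 80% needs 175 per arm. With design effect 1 + 49 × ICC, 80% is reached only for an ICC up to about 0.015 (normal) or 0.008 (t, 10 df). The ICC is not stated, so the figure cannot be reproduced. It serves below only as a base for the power cost.

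**Step 1: individual allocation stratified by rank, comparison of levels at one visit.** Let R² be the share of outcome variance explained by rank. The documents do not give it, so the values are assumptions.

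- SE overstatement without rank = 1/√(1 − R²)
- Type I error without rank = 2[1 − Φ(1.96/√(1 − R²))]
- Power without rank = Φ((d/SE − 1.96)/√(1 − R²)); with rank = Φ(d/(SE√(1 − R²)) − 1.96), where SE = √(2/n) and n is the number per arm

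| Assumed R² | SE factor | Type I error | Power at 300 per arm, without / with rank | Power at 175 per arm, without / with rank |
|---|---|---|---|---|
| 0.02 | 1.010 | 0.048 | 0.958 / 0.960 | 0.804 / 0.809 |
| 0.05 | 1.026 | 0.044 | 0.961 / 0.965 | 0.807 / 0.821 |
| 0.10 | 1.054 | 0.039 | 0.965 / 0.972 | 0.814 / 0.841 |
| 0.20 | 1.118 | 0.028 | 0.972 / 0.984 | 0.828 / 0.881 |

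The power lost is at most about 1.2 points at 300 per arm, and about 0.5 to 5 points where power is near 80%.

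**Step 2: the primary contrast, which is change.** If rank shifts a soldier's score equally at every visit, the shift drops out of follow-up minus baseline. The R² that matters is then the share of the variance of change that rank explains. A simulation checked this with 600 soldiers, three equal rank bands, 1:1 allocation within band and 5,000 runs. Its Monte Carlo error near 0.05 is √(0.05 × 0.95/5,000) ≈ 0.003.

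- Rank affects level only (R² about 0.10): type I error of the change contrast without rank is 0.050.
- Rank also modifies change, by 0.3 per band on an outcome with SD about 1: type I error is 0.046. The formula gives a similar answer. The rank variance in change is 0.3² × 2/3 = 0.06, the residual variance is 0.8, so R² = 0.06/0.86 = 0.07 and type I error is about 0.042.

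**Step 3: whole groups randomised, 6 per arm.** Assume that the officer share varies between groups with SD s = 0.10 to 0.20. The chance difference in officer share between arms has SD s√(2/6). If officers score 0.5 SD higher (assumption), the chance difference in level has SD 0.10 × 0.577 × 0.5 = 0.029 to 0.20 × 0.577 × 0.5 = 0.058, or 10% to 19% of d = 0.30. This too is a level difference, present at baseline and at follow-up. For the change contrast, the 0.5 must be replaced by the officer difference in change. Each 0.1 SD of that gives one fifth of the figures above, 0.006 to 0.012 SD.

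**Step 4: deployed-only analysis.** Stratification fixes rank balance among all those randomised. It does not fix it in a subset defined afterwards by deployment. Whether deployment varies with rank is not stated.

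**Step 5: bands against eligibility.** Eligible: any soldier aged 18 or older, with no exclusions. Bands: E-4 to E-6, E-7 to E-9, officers. Left over: E-1 to E-3.

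**The case against.** Four points can be made against this.

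1. *The effect is small and in the safe direction.* This stands. Omission does not bias a rank-stratified comparison. A reader might infer from the 4.4% to 3.9% type I error at R² of 0.05 to 0.10, or from an imbalance of 10% to 19% of the target effect, that the primary test is materially affected. The documents do not support that: those figures describe a comparison of levels, and the primary outcome is change.

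2. *A condensed article may leave covariates to the analysis plan.* This stands in part. A fuller plan could add rank, and the article does not say that its list is complete. But it does list the model terms and names a covariate, so suggesting rank improves on what is stated.

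3. *The gap below E-4 may be empty in practice.* A reader might infer that the fallback to Brigade Combat Teams will bring such soldiers in. The article gives no rank composition for those units, and the same sentence seeks units resembling the first brigade, whose members are described as senior. So the number may be small. The mismatch between eligibility and bands remains.

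4. *The unit of randomisation comes first.* This stands. Sections 2.2.1 and 2.4 describe incompatible schemes, and if groups are randomised, participant-level rank strata cannot be applied as written. The absence of a named group (cluster) effect, when power was computed for 12 clusters, is then a separate and larger matter. It does not remove the case for rank as a covariate.

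**Conclusion.** The point holds, at minor severity. Rank is named as a stratification factor and is missing from the stated model. Under stratified individual allocation the cost is slight conservatism and a little precision, mainly if rank modifies change over time. Type I error for the change contrast was 0.050 with a level effect only and 0.046 with the assumed rank-by-time effect. Under group randomisation, rank mix is left to chance, and in the deployed-only analysis balance is not guaranteed under either scheme. Every magnitude rests on assumed rank effects, because the article gives none. The bands and the eligibility rule do not match for E-1 to E-3, with unknown and possibly small practical effect.

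**What to change.** 1. First reconcile sections 2.2.1 and 2.4 on whether groups or individuals are randomised.
2. Add rank (three levels) and rank by time as fixed effects in the primary and supplementary models. If individuals are randomised, rank enters as the stratification factor. If groups are, it enters as a baseline covariate.
3. Align the bands with eligibility, for example by defining the lowest band as all enlisted grades up to E-6.

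The cost is two lines of analysis wording and one line in the allocation rule. With the five scheduled assessments and time as categories, rank adds 2 parameters and rank by time adds 2 × 4 = 8, so 10 in all or 2 per visit. No new data are needed, since stratifying as section 2.4 describes already requires each participant's rank.

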### Consent

2.5

An authorized and trained member of the research team engages potential participants in an interactive explanation of the study guided by the informed consent document. Individual informed consent is obtained following recruitment briefings or at another time when a member of the research team can meet with interested individuals. Soldiers who are not interested in participating in the study continue with unit training as usual.

### Measures

2.6

Ideally, resiliency enhancement training for military personnel demonstrates not only improvements in self-reported resiliency and other related constructs but also demonstrates positive adaptation in the face of significant stress or adversity as a result of the training (33). Related to this, the present study examines a range of resilience-related constructs (i.e., dispositional recovery, stress response, and grit) and correlates (dysfunctional cognitions, depression, and anxiety). Given our theoretical approach, we anticipate that resilience-related outcomes would be associated with increased psychological flexibility (16). The schedule of assessments is outlined in Table 1. A brief description of each measure is provided below. A more detailed description of each measure including information on validity and reliability of each measure is included in Supplement 1. Administered assessments address the constructs of psychological resilience, trait resilience, psychological flexibility, self-efficacy, mindset, life satisfaction, psychological health, unit cohesion, family functioning, and evaluation and feedback about the training (see Table 1).

**Table 1 tab1:** Schedule of assessments involved in the Resilience and Readiness Optimization/Enhancement (R2OE) study.

Construct	Assessment	Number of items	Baseline	Every 4 months
Psychological resilience	Connor-Davidson Resilience Scale (CD-RISC)	10	X	X
	Dispositional Recovery and Dysfunction Inventory (DRDI)	14	X	X
	Response to Stressful Experiences Scale (RSES)	22	X	X
Trait resilience	Short Grit Scale (Grit-S)	8	X	X
Psychological flexibility	Acceptance and Action Questionnaire-II (AAQ-2)	7	X	X
	Multidimensional Psychological Flexibility Inventory	60	X	X
Self-efficacy	General Self-Efficacy Questionnaire–6 (GSEQ-6)	6	X	X
Mindset	Implicit Theories of Intelligence Scale (ITIS)	6	X	X
Life satisfaction	Quality of Life Scale	16	X	X
Psychological health	Generalized Anxiety (GAD-7)	7	X	X
	PTSD Checklist (PCL-5)	20	X	X
	Patient Health Questionnaire-9 (PHQ-9)	9	X	X
Unit cohesion	Walter Reed Army Institute for Research (WRAIR) Military Vertical and Horizontal Cohesion Scale	15	X	X
Family functioning	General Functioning Scale (GF12)	12	X	X
Evaluation and feedback about training	Qualitative Interview			2-weeks after training

Assessments will be conducted at baseline and every 4 months thereafter for a total of 16 months.

